### Secondary outcomes

All other cognitive, biomarker, mood, wellness and exercise measures will be treated as secondary outcomes. Mixed design, repeated measures analysis of covariance (ANCOVA) will be used to assess treatment-related changes in all secondary outcomes over the study. Hierarchical regression will be used to establish the relationship between change in biomarkers and changes in cognitive function. Secondary analysis will examine the pooled effects of the two intervention arms involving the Mediterranean diet versus the control arm and the two intervention arms involving exercise versus the control arm.

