## Sample size

To date no studies using specific measures of cognition more sensitive than the MMSE have investigated the cognitive effects of a Mediterranean dietary intervention in the elderly. However, numerous trials have examined the effects of exercise fitness interventions. In a meta-analysis conducted to investigate the potential for fitness training to improve cognition in sedentary, but otherwise healthy, older adults, fitness training increased cognitive performance 0.5 SD on average, regardless of the type of cognitive task or the training method [27]. Using Cohen’s effect size criteria, this represents a medium effect size [65]. Although there are no relevant trials which have focussed on the Mediterranean diet, from which to determine an effect size, we have previously identified slightly larger effect sizes on SUCCAB memory measures following several months combined micronutrient, mineral and herbal supplementation in older people with risk factors for cognitive decline [66, 67]. We would anticipate the dietary change condition may exert many of the same benefits as micronutrient dietary supplementation, therefore a comparable effect size may be anticipated. Power analysis was conducted using GPower 3.1.3 to determine the sample size required for a four armed intervention (exercise change only, diet change only, exercise and diet change, no change) using an analysis of variance (ANOVA) design. It was indicated that a total sample of 128 participants would be required to detect a moderate effect size (*f* = 0.30), power of 80 % and a significance level of 5 %. Based on previous trials conducted by the Swinburne University Centre for Human Psychopharmacology, an allowance for a 15 % drop out from the trial has been factored in. Therefore, a total sample of 148 participants will be recruited for this trial, with 37 individuals randomised to each arm of the study.

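### The pooled secondary contrasts compare diet-containing and exercise-containing arms with control alone, so neither isolates diet or exercise: each carries half of the other intervention's effect

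*Protocol article*

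**What the plan says.** The Protocol article (Sample size) describes a "four armed intervention (exercise change only, diet change only, exercise and diet change, no change", which is every combination of two interventions, each present or absent. Arms are equal, "with 37 individuals randomised to each arm of the study".

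Under Analysis, Primary outcome, a repeated measures ANCOVA assesses treatment-related change in cognitive performance. Under Analysis, Secondary outcomes, the article adds two pooled comparisons. The one for diet reads: "Secondary analysis will examine the pooled effects of the two intervention arms involving the Mediterranean diet versus the control arm". The one for exercise has the same form: "the two intervention arms involving exercise versus the control arm". Both name the control arm alone as comparator. The exercise-only arm has no part in the diet comparison, the diet-only arm has none in the exercise comparison, and no adjustment for the other intervention is described.

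Aims and study hypotheses expects each intervention to outperform control and the combined arm to do best. The Conclusion states the hypothesis as one about each intervention independently as well as together.

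**The concern.** Pooling arms by component invites the reader to take the result as the effect of that component. The contrast cannot bear that reading. The diet-containing group is half diet-only and half diet plus walking, while the comparator does neither, so the groups differ in walking as well as in diet. The exercise contrast is the mirror image, and the combined arm sits on the active side of both.

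On the trial's own hypothesis both interventions work, so the carry-over is to be expected. A statement that the Mediterranean diet improves a secondary outcome could then be produced wholly or partly by walking, and the reverse.

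**Working it through.** **Inputs (Protocol article, Sample size).** Four equal arms. The target is stated as "a total sample of 128 participants would be required to detect a moderate effect size", with Cohen's f given as 0.30. The test is specified at "power of 80 % and a significance level of 5" per cent. For losses, "an allowance for a 15 % drop out from the trial has been factored in". For exercise, "fitness training increased cognitive performance 0.5 SD on average". The target of 128 gives 128/4 = 32 per arm; recruitment gives 148/4 = 37 per arm.

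**The plan's own figure.** One-way ANOVA with four groups, noncentrality N x f^2, 3 numerator degrees of freedom: the smallest N for 80% power is 126, or 128 with equal arms, where power is 0.810. The 128 reproduces. It belongs to the four-group test; no figure is stated for the pooled contrasts.

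**Expected values.** Let the arm means, in SD units relative to control, be C = 0, E = e, D = d and DE = d + e + i, where i is the interaction.

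- Diet contrast as written: (D + DE)/2 - C = d + e/2 + i/2.
- Balanced diet contrast: (D + DE)/2 - (C + E)/2 = d + i/2.
- Difference: (C + E)/2 - C = e/2, whatever the value of i.

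By symmetry, the exercise contrast as written estimates e + d/2 + i/2, and its balanced form e + i/2.

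**Size, with i = 0.**

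- e = 0.5, d = 0: the written diet contrast averages 0 + 0.5/2 = 0.25 SD; the balanced one averages 0.
- e = 0.3, d = 0: 0.15 SD against 0.
- e = d = 0.5: 0.5 + 0.25 = 0.75 SD against 0.50 SD.

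**Standard errors (SD = 1, n per arm).**

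- Written: sqrt(1/(2n) + 1/n). With n = 32, sqrt(1/64 + 1/32) = 0.217; with n = 37, 0.201.
- Balanced: sqrt(1/(2n) + 1/(2n)). With n = 32, sqrt(1/64 + 1/64) = 0.177; with n = 37, 0.164.
- Ratio: sqrt(1.5) = 1.22, because the written contrast leaves one arm out.

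**Rejection rates (two-sided 5%, noncentral t, variance pooled over four arms), d = 0 and i = 0.**

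| Exercise effect | n per arm | Written diet contrast | Balanced diet contrast |
|---|---|---|---|
| 0.5 SD | 32 | 20.9% | 5.0% |
| 0.5 SD | 37 | 23.4% | 5.0% |
| 0.3 SD | 32 | 10.6% | 5.0% |
| 0.3 SD | 37 | 11.5% | 5.0% |

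A simulation of 200,000 trials at 0.5 SD and 32 per arm gave 21.2% and 5.0%, using a normal critical value.

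**Overlap.** With equal arms, the two written contrasts have covariance (1 + 0.25)/n and variance 1.5/n each, so they correlate at 1.25/1.5 = 0.83. They say little separately about the two components.

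**Interaction.** DE - D - E + C has standard error sqrt(4/32) = 0.354 SD. An interaction of 0.5 SD gives a noncentrality of 0.5/0.354 = 1.41, or about 29% power.

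**The case against.** The strongest defence is that the article never calls these contrasts main effects. It describes pooled arms against control, which is a legitimate comparison of having a diet-containing (or exercise-containing) programme with having none. That stands: the contrast is valid for that question, and the fault lies in reading it as a component effect.

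Three stronger readings are tempting but not supported.

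- A reader might infer that the trial cannot answer its main question. The pooled contrasts are secondary. The primary ANCOVA uses the four randomised groups, within which diet-only versus control and exercise-only versus control are free of the other intervention. The 128 and 148 do not rest on pooling.
- A reader might take the 21% as inflated type I error of the test as written. If exercise works, diet-containing arms and control truly differ, so that null hypothesis is false. The figure is an error rate only when the result is attributed to diet.
- A reader might infer a loss of power from the larger standard error: for a contrast of 0.5 SD, 63% against 80% at 32 per arm. Both contrasts equal 0.5 SD only in special cases, such as an exercise intervention that does nothing, and then there is no carry-over. With both effects at 0.5 SD and additive, the written contrast rejects in 93% of trials against 80%, because it tests a larger, mixed quantity. The standard errors compare fairly; the powers do not.

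The balanced contrast also has a limit. It estimates d + i/2, so it equals the diet effect in the absence of exercise only if there is no interaction, and the article's background (Cognition and combined exercise and diet) raises synergy. The written contrast carries the same i/2 in addition to e/2, so it offers no protection.

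**Conclusion.** The point holds as a should-fix matter confined to the secondary analysis. The stated contrasts do not separate diet from exercise: with equally weighted arms, each carries exactly half of the other intervention's effect, with or without interaction. At the protocol's 0.5 SD for exercise and an inert diet, that is 0.25 SD, and about 21% of trials with 32 per arm (23% with 37) would credit diet with an effect it does not have, if the result is read that way. The standard error is about 22% larger than that of the balanced contrast.

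The exact half assumes equal arm sizes; with unequal completion it becomes the combined arm's share of the pooled group. The rejection rates further assume no interaction, an outcome SD of 1 without gain from baseline adjustment, and independent participants, so the allocation of cohabiting couples together is ignored. The 0.5 SD is the protocol's figure for cognitive performance, used here as an illustration for any secondary outcome.

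**What to change.** Amend the sentence under Analysis, Secondary outcomes, or supplement it in the analysis plan, before results are seen:

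- Diet effect: diet plus combined versus control plus exercise.
- Exercise effect: exercise plus combined versus control plus diet.
- Estimate both from one baseline-adjusted model of all four arms.
- Report alongside them the diet-by-exercise interaction with its confidence interval, and the diet-only and exercise-only estimates against control.
- If the pooled-versus-control contrasts are kept, label them as any diet-containing (or any exercise-containing) programme versus none, and do not attribute them to one component.

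The change needs no new data or participants. Its cost is interpretive: the balanced contrasts depend on the interaction, which this trial estimates imprecisely (standard error about 0.35 SD, about 29% power for 0.5 SD at 32 per arm). A non-significant interaction test should therefore not be taken as proof of additivity, which is why the single-arm estimates belong beside the balanced ones.

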## Conclusion

With the rapid ageing of the global population and the commensurate increase in age related cognitive decline, there is an exigent need for broadly available and easily implemented public health interventions that are aimed at ameliorating this issue. There is support for the efficacy of both the Mediterranean style of diet and aerobic exercise interventions in positively affecting cognitive performance in older adults. However, at present, much of the evidence is observational or not balanced by the use of control groups. Additionally, there has been little use of sensitive cognitive measures, covering multiple, specific cognitive domains. Finally, also lacking in the current literature is investigation into the possible mechanisms by which the observed improvements in cognition through diet and exercise, either individually or in combination, may be being achieved. The current trial aims to use clinical trial methodology to test the hypothesis that both Mediterranean diet and walking based aerobic exercise, both independently and in combination, will improve cognitive performance in older people living independently in aged care facilities. Additionally, through blood biomarker, cardiovascular and psychological assessments, this study aims to investigate possible mechanisms by which such improvements may be being achieved. The potential to ameliorate the rate of cognitive decline in older people through achievable lifestyle change may be of substantial importance to public health in an increasingly ageing society.

## Abbreviations

LIILAC: Lifestyle intervention in independent living aged care
ANZCTR: Australia and New Zealand Clinical Trials Registry
AD: Alzheimer’s disease
APOE: Apolipoprotein E
BDNF: Brain derived neurotrophic factor
MCI: Mild cognitive impairment
CRP: C-reactive protein
MMSE: Mini mental state examination
GDS: Geriatric depression scale
SUCCAB: Swinburne University Computerised Cognitive Assessment Battery
LFT: Liver function test
HbA1c: Haemoglobin A1c
IGF-1: Insulin-like growth factor
DASS: Depression anxiety stress scale
POMS: Profile of Mood State
GHQ: General Health Questionnaire
CHAMPS: Community Health Activities Model Program for Seniors
